**Table 1: Outcome Measures**

|               | Test 1
(day# 2 [+/-1])
(before therapy) | Test 2
(day# 5 [+/-1]) | Test 3
(day# 9 [+/-1])
(after therapy) | Test 4
(day## 90[+/-5])
(phone contact) |
|---------------|-----------------------------------------------|---------------------------|----------------------------------------------|-----------------------------------------------|
| TCT           | X                                             | X**                       | X                                            |                                               |
| NIHSS         | X                                             |                           | X                                            |                                               |
| CBS           | X*                                            | X*                        | X*                                           |                                               |
| MESUPES       | X*                                            | X*                        | X*                                           |                                               |
| mRS           | X                                             |                           | X                                            | X                                             |
| Barthel Index | X                                             |                           | X                                            | X                                             |

Day # = day after admission to hospital

Day ## = day after stroke onset

X\* = Assessment before and after therapy

X\*\* = Assessment only after therapy

TCT = Trunc Control Test

NIHSS = National Institutes of Health Stroke Scale

CBS = Catherine Bergego Scale (item 5 and 6) (=Neglect Test)

MESUPES = motor evaluation scale for upper extremity in stroke patients (item 1 to 4 = MESUPES arm)

mRS = modified Rankin Scale

**Table 2: trial schedule**

|                                    | Screening visit | Baseline visit | Follow up visits |              |              |               |
|------------------------------------|-----------------|----------------|------------------|--------------|--------------|---------------|
| Procedures                  | 1) Screening    | 2) Enrollement | 3) Test 1        | 4) Test 2    | 5) Test 3    | 6) Test 4     |
|                                    | day 1-3         | day 1-3        | day 2(+/-1)      | day 5 (+/-1) | day 9 (+/-1) | day 90 (+/-5) |
| Check inclusion/exclusion criteria | X               | X              |                  |              |              |               |
| Randomisation                      |                 | X              |                  |              |              |               |
| Informed consent                   |                 | X              |                  |              |              |               |
| Clinical examination               | X               | X              | X                | X            | X            |               |
| Medical history                    | X               |                |                  |              |              |               |
| Demographic data                   | X               |                |                  |              |              |               |
| Concomitant medication             |                 | X              |                  |              | X            | X             |
| Adverse events                     |                 | X              | X                | X            | X            | X             |
| Imaging (CCT/MRI)                  | X               |                |                  |              |              |               |
| NIHSS                              | X               |                | X                |              | X            |               |
| mRS                                | Premorbid-mRS   |                | X                |              | X            | X             |
| CBS (5+6) (neglect test)           |                 |                | X                | X            | X            |               |
| MESUPES arm (1-4)                  |                 |                | X                | X            | X            |               |
| Trunc Control Test (TCT)           |                 |                | X                | X            | X            |               |
| Barthel Index                      |                 |                | X                |              | X            | X             |

CCT=cranial computed tomography. MRI=magnetic resonance imaging. CBS=Catherine Bergego scale (item 5 and 6) (=Neglect Test). MESUPES= motor evaluation scale for upper extremity in stroke patients (item 1 to 4 = MESUPES arm).

**Figure 1: time schedule**

[figure not shown]

## 10. Outcome Assessments

### 10.1 Detailed description of assessment tools

#### *(i) Trunc Control Test (TCT)* 

The TCT examines 4 items of axial movements:

- 1) rolling from a supine position to the weak side;
- 2) rolling from a supine position to the strong side;
- 3) sitting up from a lying-down position; and
- 4) sitting in a balanced position on the edge of the bed with feet off the ground for 30 seconds.

For each item can be scored 0, 12 or 25 points:

- 0= unable to perform movement without assistance;
- 12= able to perform movement, but in an abnormal style (Examples: pulls on bed clothes or monkey pole, or uses arms to steady self when sitting);
- 25= able to complete movement normally.

For the sitting balance item, a patient scores 12 if he needs to touch anything with his hands to stay upright, and 0 if he is unable to stay up (by any means) for 30 seconds. The TCT score is the sum of the scores obtained on the four tests and ranges from 0 (minimum) to 100 (maximum and indicating better performance). The examiner's score must relate solely to the performance during the test.

#### *(ii) National Institutes of Health Stroke Scale (NIHSS)* 

The NIHSS measures the severity of symptoms associated with cerebral infarcts and used as a quantitative measure of neurological deficit post stroke. The score was originally designed to assess differences among clinical trial interventions  and is compound out of 15 items assessing severity of impairment in different neurological systems (level of consciousness, speech, motor function, ataxia, sensory loss and others). Items are graded on a 3 or 4 point ordinal scale; a score of 0 typically indicates normal function in that specific ability. Score ranges from 0 to 42, higher scores indicating greater severity. Stroke severity may be stratified on the basis of NIHSS scores as mild (NIHSS 1-5), mild to moderately severe (NIHSS 5-14), severe (NIHSS 15-24) and very severe (NIHSS >25) .

#### *(iii) Catherine Bergego Scale (CBS) (=Neglect Test)* 

The Catherine Bergego Scale is a standardised checklist to assess the presence and extent of neglect in patients with stroke and hemispatial neglect. The scale also provides a measure of neglect self-awareness (anosognosia). While the authors of this scale specify use of the CBS with patients with right hemispatial neglect, we will use this scale without modification for individuals with left hemispatial neglect. A functional scale consisting of 10 items related to neglect in everyday life (such as dressing, washing, eating, communicating, exploratory activities and moving around) is used. The CBS uses a 4-point rating scale to indicate the severity of neglect for each item, scoring 0 for no neglect, 1 for a mild neglect (patient always explores the right hemispace first and slowly or hesitantly explores the left side), 2 for a moderate neglect (patient demonstrates constant and clear left-sided omissions or collisions) and 3 for a severe neglect (patient is only able to explore the right hemispace). This results in a total score out of 30.

The therapist scores the patient on the following items:

1. Forgets to groom or shave the left part of his/her face
2. Experiences difficulty in adjusting his/her left sleeve or slipper
3. Forgets to eat food on the left side of his/her plate
4. Forgets to clean the left side of his/her mouth after eating
5. Experiences difficulty in looking towards the left
6. Forgets about a left part of his/her body (e.g. forgets to put his/her upper limb on the armrest, or his/her left foot on the wheelchair rest, or forgets to use his/her left arm when he/she needs to)
7. Has difficulty in paying attention to noise or people addressing him/her from the left
8. Collides with people or objects on the left side, such as doors or furniture (either while walking or driving a wheelchair)
9. Experiences difficulty in finding his/her way towards the left when traveling in familiar places or in the rehabilitation unit
10. Experiences difficulty finding his/her personal belongings in the room or bathroom when they are on the left side

The CBS takes approximately 30 minutes to administer. In order to save time and to spare our patients we abbreviated the CBS and assessed only items 5 and 6. This results in a total score of 6 (0 no neglect, 6 severe neglect).

**(iv) Motor Evaluation Scale for Upper Extremity in Stroke Patients (MESUPES):** 

The MESUPES is a objective evaluation scale designed to assess quality of movement of arm and hand function after stroke. The MESUPES was developed for use with adults with stroke. The scale consists of 17 items divided into two subscales: the MESUPES-Arm function with 8 items (scores 0-5) and the MESUPES-Hand function with 9 items (scores 0-2). With all items the test has a total score of 58 and a duration of 30 minutes. The MESUPES-Arm with 8 items has a total score of 40. The first four items are performed in supine; all other items are performed in a sitting position with hips and knees in 90° flexion and elbows on the table. The patient cannot be assessed if he cannot maintain an upright position for the tasks in sitting position. For this reason we decided to perform only items 1 to 4 in our trial, because the majority of patients with severe hemiparesis is not able to maintain an upright position in the early phase.

Items 1 to 4 start in a supine position, the head resting on a pillow, a small cylindrical pillow placed under the knees to support the legs, arms extended and resting on the table, forearms in pronation, fingers in a relaxed extended and adducted position. The patient is requested:

- 1) to put the hand on the stomach (score 0 to 5)
- 2) to put the hand back to the starting position (score 0 to 5)
- 3) to abduct the arm 0°-90° (arm extended, forearm in neutral position) (score 0 to 5)
- 4) to put arm back to the starting position (score 0 to 5).

The execution of these 4 items are scored in three consecutive phases:

- A) *Passive score*: The task is performed passively and tone is evaluated (score 0 for hyper- or hypotonus and score 1 for an adequate adaption to the tone meanwhile the movement).
- B) *Assisted score*: The therapist performs the movement while the patients assists and the presence of normal muscle contractions is scored (score 2)
- C) *Independent score*: The patient performs the movement by himself and the range of motion that is executed in a qualitatively normal way is scored (score 3 if patient

performs part of the movement; score 4 if patient performs the entire movement but slowly or with big effort; and score 5 if patient performs movement in normal speed).

The therapist should wait until tone is normalized before starting a new task. If the patient is not able to achieve a relaxed starting position, he is awarded a score of 0 for the item. A total score of 20 can be achieved with a range of 0 indicating no movement and no tonus adaption to a passive movement to 20 indicating an independent arm movement.

**(v) Modified Rankin Scale (mRS)  :**

The modified Rankin Scale is a single-item global outcomes rating scale that categorises level of functional independence with reference to pre-stroke activities and is an ordinal scale ranging from 0 (*no symptoms*), 1 (*no significant disability despite symptoms; able to carry out all usual duties and activities*), 2 (*slight disability: unable to carry out all previous activities but able to look after own affairs without assistance*), 3 (*moderate disability: requiring some help, but able to walk without assistance*), 4 (*moderately severe disability: unable to walk without assistance, and unable to attend to own bodily needs without assistance*), to 5 (*severe disability: bedridden, incontinent, and requiring constant nursing care and attention*), with a score of 6 allocated to those who die. Assessment is carried out by asking the patient about their activities of daily living, including outdoor activities.

**(vi) Barthel ADL Index (BI)  :**

The Barthel scale or Barthel activities of daily life (ADL) index is a valid measure of disability. 10 items of daily life and mobility activity are assessed, including feeding, bathing, grooming, dressing, bowel control, bladder control, toileting, chair transfer, mobility and stair climbing. Items are rated based on the amount of assistance required to complete each activity. Each performance item is rated on this scale with a given number of points assigned to each level or ranking. A higher score is associated with a greater likelihood of being able to live at home with a degree of independence. There are several possible scoring techniques for the BI. The originally described index was scored in five-point increments, giving a score of 0-100. Collin et al. felt that this gave a misleading impression of its accuracy and so rescored it in one-point increments, giving a total score ranging from 0-20, with lower scores indicating increased disability. Each item is rated in terms of whether the patient can perform the task independently, with some assistance, or is dependent on help based on observation. In this trial we used the 20 point scale, because we had a validated German version for phone interview with a 20 point scale.

**(vii) Medical Research Council Scale :**

Motor power for inclusion criteria was measured using the Medical Research Council scale, grading from power 5 (normal power) to 0 (no contraction) and differing between diminished power, movement against gravity, movement with gravity eliminated and flicker or trace contraction when attempting movement scoring 4,3,2 and 1, respectively.

## 10.2: Summary for assessment tools:

- The TCT is a validated test to assess motor impairment and postural control after stroke. A range of 0 (patient is not able to turn around at all in lying position) to 100 (patient is able to sit for 30 seconds independently on the edge of the bed) points can be achieved.
- The NIHSS is used as a quantitative measure of neurological deficit in stroke patients. The 15 items score ranges from 0 to 42, higher scores indicating a more severe neurological deficit and a greater stroke severity.

- The CBS is a standardised checklist consisting of 10 items to assess the presence and extent of neglect in patients with stroke and hemispatial neglect, using a 4 point rating scale for each item (0 indicating no neglect and 3 indicating a severe neglect). In order to save time and to spare our patients we abbreviated the CBS and assessed only item 5 and 6. This results in a total score of 6 (0 no neglect, 6 severe neglect).
- The MESUPES is a clinical and research tool to qualitatively evaluate arm and hand function during recovery after stroke, comprising of 17 items pertaining to arm (8 items) and hand (9 items) performance. The whole tests takes up to 30 minutes, wherefore we performed in our trial items 1 to 4 of the MESUPES-arm. Furthermore only the first 4 items are performed in lying position, so that even severe effected patients were able to perform the task. A total score of 20 can be achieved with a range of 0 (indication no movement and no tonus adaption to a passive movement) to 20 (indicating an independing arm movement).
- The mRS categorises level of functional independence with reference to pre-stroke activities and is an ordinal scale ranging from 0 (no symptoms) to 5 (severe disability), with a score of 6 allocated to patients who died.
- The BI is a validated measure of disability assessing 10 items of daily life and mobility activity with a total score ranging from 0-20 (lower scores indicating increased disability, 20 indicating all activities performed).

### 10.3 General comment:

The selection of the primary outcome parameter is a challenge in every clinical trial, but especially in rehabilitation trials, with a plenty of different assessment tools used in RCTs. In our opinion postural control is an important prerequisite for further mobility which was the reason to choose the TCT as primary outcome parameter. The early control of sitting balance as tested with the TCT as a base for regaining standing balance and afterwards gait is an important factor for the final outcome at six-months. We include the mRS and BI as a secondary outcome, although the European Stroke Organisation Outcomes Working Group recommended the use of the mRS as a primary outcome measure in acute stroke trials. In the preperation of this trial we made a big effort to identify a probable assessment tool to objectify the hemispatial neglect, which is (together with aphasia, which was excluded) one of the most prominent focal cognitive deficits after stroke in clinical practice. Due to feasibility in daily clinical routine and under consideration of the reduced resilience of acute stroke patients we choose the CBS as a standardized checklist to assess the presence and extent of neglect in patients with stroke and hemispatial neglect. We selected assessment tools that are feasible in clinical routine and do not lead to an additional burden for the stroke patients.

## **11 Sample size and statistical analysis plan:**

### 11.1 Sample size

This is a pilot trial. Vojta therapy has never been investigated in stroke patients. A sample size calculation for this pilot trial was not feasible, because desired parameters, as the estimated effect size or the standart deviation due to missing prior information or data in the literature could not be estimated. For feasability reasons we choose a sample size of 40 subjects (20 in each group) in order to complete recruitment in this monocentric trial within one to 1,5 years.

### 11.2 Statistical analysis plan

We plan an intention to treat analysis. For the primary endpoint (difference of scores in trunc control test between day 9 and baseline) an increase of 12 points (=12%) on the scale of the TCT was predefined as a meaningful difference pragmatically, due to lack of data in the literature, because an improvement of 12 points in the TCT indicates a clinical relevant improvement of self-dependence (i.e. no more need of an auxiliary person, no more need for an adjuvant as edge of bed for moving). Normal distribution of the variables will be tested by the Shapiro-Wilk-test. For the primary endpoint we assume non-Gaussian distribution and we plan an analysis of variance with the non-parametric Mann–Whitney-U-test. The primary endpoint (difference of scores in trunc control test between day 9 and baseline) will be tested concerning the influencing factors a priori known to potentially affect outcome (age, sex, NIHSS > or <10 at baseline; stroke site, thrombolysis and thrombectomy) to test whether they affected the treatment. Complications occurring between baseline and day 9 will be analyzed with the exact Fisher Test. An interim analysis is not planned. We have not defined any discontinuation criteria. Statistical analysis will be made by the principal investigator with support of a statistical institute.

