## 6. Screening and Randomisation:

All potentially eligible patients are screened on the first day after admission to the stroke unit and during the first 72h after stroke onset, in case of deterioration after admission. Eligible patient with written informed consent will be enrolled and randomly assigned (1:1) to receive usual stroke unit care with conventional physiotherapy (control group) or Vojta therapy (interventional group).

| Arm                  | Therapy                    |
|----------------------|----------------------------|
| interventional group | Vojta therapy              |
| control group        | conventional physiotherapy |

Randomisation will be performed with sealed, opaque and sequentially numbered envelope. The investigators are instructed to assign the patient according to the envelope with the lowest randomisation number. Randomisation has to be done within 72 hours after onset of symptoms or after patients were last seen well and can be done by a physiotherapist or the investigator, who enrolles the subject. Stratification for stroke severity was disclaimed due to the small sample size.

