## **8. Predefined Outcome Measures**

### **8.1. Primary Outcome Measure:**

Improvement of postural control measured with the trunc control test (TCT) on day 9 after admission to the hospital compared to baseline (Difference in scores on TCT scale between baseline and day 9)

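### The primary Mann-Whitney test on TCT change is valid but does not condition on baseline TCT, and the 12-point threshold is not defined as within-patient or between-arm

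*Protocol*

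**What the plan says.** Protocol section 8.1 defines the primary outcome as a change score: "Difference in scores on TCT scale between baseline and day 9". Section 11.2 then names the test: "For the primary endpoint we assume non-Gaussian distribution and we plan an analysis of variance with the non-parametric" Mann-Whitney U test. No covariate enters that test.

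The same section says the primary endpoint will also be examined against a list of factors: "age, sex, NIHSS > or <10 at baseline; stroke site, thrombolysis and thrombectomy". Baseline TCT is not on the list. The stated purpose is to see whether the factors affected the treatment, so this is a separate analysis and does not adjust the primary comparison.

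On relevance, section 11.2 says that "an increase of 12 points (=12%) on the scale of the TCT was predefined as a meaningful difference pragmatically". The reason given is what an individual patient regains in independence.

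On design, section 6 says "Stratification for stroke severity was disclaimed due to the small sample size", and section 11.1 says "we choose a sample size of 40 subjects (20 in each group", chosen for feasibility in a pilot trial. Section 9 has TCT measured at day 2 before the first treatment, so the baseline value exists for every patient who can be tested.

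**The concern.** A change score takes the baseline off with a fixed slope of 1. If the true slope of day-9 TCT on baseline TCT differs from 1, the change still depends on where the patient started. Two things follow. Variance that the baseline could explain stays in the comparison. And if one arm happens to start lower, part of that imbalance passes into the estimated effect. Both matter most in a small, unstratified trial, which is the situation here.

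The second issue is the 12 points. Section 10.1 scores each of the four TCT items 0, 12 or 25, so 12 points is one step up on one item. Read as a patient's own increase, it is a response that early spontaneous recovery could produce in both arms, and reaching it says nothing about Vojta therapy. Read as a difference between arms, it is a benchmark for the trial result. The protocol does not say which is meant.

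**Working it through.** **Inputs from the protocol.** 20 patients per arm, 1:1 (sections 6 and 11.1); endpoint is the TCT change to day 9 (8.1); scale 0 to 100 from four items scored 0, 12 or 25 (10.1); threshold 12 points (11.2).

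**Inputs not in the protocol.** Section 11.1 states "A sample size calculation for this pilot trial was not feasible", with parameters such "as the estimated effect size or the standart deviation due to missing prior information or data in the literature could not be estimated". There is therefore no planned power figure to reproduce. The SDs and correlations below are assumptions, shown over a range. Two-sided 5% is also assumed.

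**Step 1. Variance with and without adjustment.** Let ρ be the correlation between baseline and day-9 TCT, and k the ratio of the day-9 SD to the baseline SD. In units of the baseline variance:

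- change score: 1 + k² − 2ρk
- day-9 score adjusted for baseline: k²(1 − ρ²)
- change minus adjusted: (1 − ρk)², which is never negative

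So adjustment cannot increase this variance, and the gain vanishes when ρk = 1. For k = 1 the ratio is (1 − ρ²)/[2(1 − ρ)] = (1 + ρ)/2. Adjusted variance divided by change-score variance:

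| k | ρ = 0.5 | ρ = 0.6 | ρ = 0.7 |
|---|---|---|---|
| 1.0 | 0.75 | 0.80 | 0.85 |
| 1.2 | 0.87 | 0.92 | 0.97 |
| 1.4 | 0.94 | 0.98 | 1.00 |

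Example for k = 1.2, ρ = 0.5: 1.44 × 0.75 / (1 + 1.44 − 1.2) = 1.08/1.24 = 0.87. At k = 1, the 40 patients carry the information of 40/0.75 = 53, 40/0.80 = 50 or 40/0.85 = 47 patients analysed by change score. That is the favourable end.

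**Step 2. Power for a 12-point between-arm difference** (k = 1, score SD 25, normal approximation).

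| ρ | SD of change, 25√[2(1−ρ)] | adjusted SD, 25√(1−ρ²) | power, change | power, adjusted |
|---|---|---|---|---|
| 0.5 | 25.0 | 21.7 | 33% | 42% |
| 0.7 | 19.4 | 17.9 | 50% | 57% |
| 0.8 | 15.8 | 15.0 | 67% | 72% |

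**Step 3. Chance imbalance.** With baseline SD 25 to 30, the difference in baseline means has SD 25√(2/20) = 7.9 to 30√(2/20) = 9.5 points. A baseline difference of 12 points or more in either direction then occurs in 13% to 21% of randomisations. With no treatment effect and an arm starting 12 points lower, the expected change-score difference in its favour is (1 − ρk) × 12. For k = 1 that is 6.0 points at ρ = 0.5 and 3.6 at ρ = 0.7. The adjusted difference is expected to be 0.

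**Step 4. Simulation on the TCT's own steps.** Four items scored 0/12/25, 20 per arm, 1,500 trials per scenario, true mean difference about 15 to 18 points, SD of change about 22 to 35. Power of Mann-Whitney on change → linear ANCOVA with baseline TCT:

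| Share scoring 0 at baseline | observed ρ about 0.4 | about 0.57 | about 0.7 |
|---|---|---|---|
| about 40% | 37.5 → 44.9% | 48.0 → 51.9% | 58.1 → 61.3% |
| 24% | 32.7 → 43.5% | 44.9 → 51.9% | 55.5 → 61.9% |
| 12% | 24.7 → 41.4% | 33.8 → 50.9% | 45.9 → 60.8% |

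The gain is 3 to 17 percentage points. Rank-based ANCOVA gave similar power (41% to 64%). With no effect, rejection rates were 3.8% to 5.9% for Mann-Whitney, 3.9% to 5.9% for ANCOVA and 4.8% to 5.8% for rank ANCOVA, all consistent with 5%.

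**Step 5. What the trial can say about 12 points.** The 95% CI half-width for the mean difference in change is 2.024 × SD × √(2/20) = 0.640 × SD. That is 9.6, 12.8 and 19.2 points for an SD of change of 15, 20 and 30, and it reaches 12 at an SD of about 19. Above that, only the interval shows which differences remain compatible with the data; a p-value does not.

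**The case against.** The strongest defence is that the planned test is legitimate. Randomisation protects its type I error, the endpoint already subtracts baseline, and a simple prespecified rank test is a reasonable choice for a pilot trial with no usable SD. Several stronger criticisms might be inferred, and the protocol does not support them.

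- *That the analysis ignores baseline TCT.* It does not; baseline is subtracted. What is missing is conditioning on it.
- *That the test is biased or its error rate inflated.* It is not. The shift in step 3 is conditional on an imbalance having occurred, and the 5% error rate already averages over such imbalances.
- *That the analysis can give no effect estimate.* A Hodges-Lehmann shift with CI can accompany a Mann-Whitney test, and a statistical analysis plan that is not shown may specify one. Its absence from the protocol is not a finding.
- *That patients near 100 cannot improve.* This is weak here. Section 5.1 requires muscle strength of grade 2 or less, and section 10.1 says most such patients cannot stay upright early on. Baseline scores should lie nearer the floor.
- *That prognostic factors are disregarded.* Section 11.2 lists several, including dichotomised NIHSS, although outside the primary test.

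What also stands is that the size of the gain is uncertain. Recovery from the floor could widen the day-9 spread and push k above 1, which moves the ratio in step 1 towards 1. In the simulations the gain was smallest (3 to 7 points) where about 40% of patients scored 0 at baseline. Nor does adjustment make a 40-patient trial well powered: in step 4 linear ANCOVA reached only 41% to 61%, for a difference larger than 12 points.

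**Conclusion.** The point holds as one of efficiency and clarity, not validity. The primary comparison leaves baseline TCT unused as a covariate in an unstratified trial of 40 patients, although the value is already collected. It therefore gives up precision and leaves chance imbalance uncorrected.

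The direction of the gain is secure, because the variance difference (1 − ρk)² cannot be negative. Its size is not secure: a 15% to 25% lower variance for ρ of 0.5 to 0.7 with equal variances, falling to practically nothing at k = 1.4 and ρ = 0.7. The simulated gain of 3 to 17 percentage points rests on assumed SDs and correlations that the protocol says it could not supply.

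Separately, the ambiguity of the 12 points is a gap in the protocol's own text and depends on none of these assumptions. The change is worth making before unblinded data are analysed, but leaving it out would not invalidate the result.

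**What to change.** In section 11.2:

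1. Make the primary analysis the between-arm comparison of day-9 TCT with baseline TCT as covariate, either by rank-based ANCOVA or by linear ANCOVA with a permutation p-value. The second option keeps the test and the estimate on the same statistic in TCT points.
2. Report the adjusted between-arm difference with its 95% CI.
3. State that the 12 points are a between-arm difference, and read the CI against that figure. If a patient-level increase is also of interest, define it separately as a responder proportion compared between arms.
4. Keep the Mann-Whitney test on change as a sensitivity analysis.

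Adjustment for baseline NIHSS as a continuous score, and the same form of analysis for the secondary outcomes, are optional.

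The cost is one degree of freedom and a few sentences, with no new data and no additional patients. Where ρk is close to 1 the adjustment brings no gain and the degree of freedom is spent for nothing, which is a negligible loss with 40 patients.
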